### Analysis plan

All the analyses will consider an alpha value threshold equal to 5% as determining the statistical significance.

Primary aims:

a. Taking into account the 12-month follow-up of the study participants, we will detect all the participants experiencing a new pneumonia event. The ratio between the number of participants experiencing one or more events and the number of participants constituing the overall sample will provide the incidence of pneumonia in the sample population. Results will be presented as pneumonia cases per 1,000 resident-days, and as pneumonia events over one year. Stratified analyses will be performed according to age groups, gender, and pre-existing pulmonary disease.

Secondary aims:

a. Primary independent variable of interest for the present analyses will be the total expenditure (in Euros) that participants will cost to the healthcare system over the follow-up year. Additional secondary analyses will also consider specific aspects of the direct healthcare costs of INCUR participants such as expenses due to hospitalizations or physical therapy sessions. All these analyses will be stratified and compared according to the presence/absence of pneumonia events.

Unadjusted and adjusted analyses of covariance, logistic regression models, and multinominal logistic regression models will be performed to evaluate the means and risks of the outcome variables predicted by the absence/presence of pneumonia events occurred during the follow-up (dicothomous independent variable of interest).

b. Participating patients will be divided in two groups, according to the presence/absence of a pneumonia event experienced during the follow-up period. Then, the risk of death will be calculated and compared between the two groups. Kaplan-Meier survival curves will be provided according to pneumonia events. Moreover, adjusted Cox proportional hazard analyses taking into account age, gender, pre-existing pulmonary disease, and other possible confounders will be performed to estimate the risk of dying in patients who experienced a pneumonia versus those who did not. Follow-up will be censored at the date of death for patients dying during the follow-up, or to the last contact date for those who did not.

c. When a pneumonia event will occur, physical function information collected after its onset will be compared to those previously recorded. The difference in physical function measured before and after the pneumonia event will be adjusted for the days between the event onset and the following physical function assessment. This analytical approach will allow to take into account the negative influence that the presence of a (sub)acute phase of the respiratory process may exert on physical function if the event will occur close to the evaluation. Mixed effects analysis of covariance models will also be performed to evaluate physical function modifications over time between patients who experienced a pneumonia event versus those who did not. If statistical power will be sufficient, stratified analyses will also be performed according to the severity of the pneumonia event (e.g., events requiring hospitalization versus those who did not).

For the present analyses, the sum of the results from the three SPPB categorized tests (ranging from 0 [worst physical performance] to 12 [best physical performance]) as well as the crude timed results obtained from each single assessment (in seconds) will be used for the analyses. This will allow to evaluate whether the pneumonia event will differently affect specific components of physical performance (i.e., balance, muscle strength, or gait/coordination).

Tertiary aims:

a. Chi-square and t-test analyses will be performed to describe the study population for main sociodemographic, behavioral, and clinical characteristics according to the presence/absence of a pneumonia event occurred during the INCUR project follow-up. Mann-Whitney U statistics will be used for non-normally distributed continuous variables. Normalization through log-transformation will be used for non-normally distributed study variables. Subsequent unadjusted and adjusted Cox proportional hazard models will be analyzed to identify patients’ characteristics that are able to significantly predict pneumonia events (dependent variable of interest). Among the covariates, age, gender, race, and preexisting respiratory conditions will always be considered as potential confounders. Age, gender, and race interactions will be tested for the studied relationships by adding specific interaction terms into the models. If possible, stratified analyses will be performed whereas significant interactions will be obtained.

A similar analytical approach will be used to evaluate specific characteristics of the EHPADs as significant determinants of pneumonia events in patients. EHPADs and patients’ characteristics might be combined in secondary analyses to evaluate the additive value of specific parameters towards the onset of pneumonia events.

b. We will perform restricted analyses in participants who will die during the follow-up (expected mortality about 20% over 12 months, that is 160 fatal events in our sample population). This subsample of participants will be divided according to the cause of death (i.e., pneumoniarelated versus other causes [expected number of cases 11.2 versus 158.8 according to Rothan- Tondeur et al [38]). Chi-square and t-test analyses will be performed to verify whether significant differences between patients dying because of a pneumonia event versus those dying for other causes exist for the following healthcare parameters: - Total expenditure (in Euros) that participants will cost to the healthcare system over the follow-up period. This datum will be obtained by the Gerontopôle from the *Caisse Primaire d’Assurance Maladie*, which has allowed the specific and exclusive release of it to the CHUToulouse. Additional analyses will also consider specific aspects of the direct healthcare costs of INCUR participants such as expenses due to hospitalizations or physical therapy sessions.

Mann-Whitney U statistics will be used for non-normally distributed continuous variables. Normalization through log-transformation will be used for non-normally distributed study variables. These analyses will consider the entire follow-up period available. Secondary analyses will also be restricted to consider the last month preceding the fatal event. In this way, we will be able to undestand whether the hypothesized higher healthcare costs of pneumonia events leading to death are distributed over time, or compressed in the very last period of life. If the statistical power will be sufficient, additional adjusted logistic and linear regression models will be performed taking into account potential confounders.

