### The INCUR study

#### Hypotheses and objectives

The INCUR project is specifically aimed at retrieving data from routine clinical practice in order to estimate the incidence of pneumonia events in older persons living in a sample of French nursing homes. Moreover, INCUR is designed to estimate the clinical and economical consequences of pneumonia events by measuring the subsequent access to medical procedures and resources. More in details, the following hypotheses have driven the rationale and conception of the INCUR project:

Primary hypotheses:

a. Pneumonia is a clinical condition frequently complicating the nursing home stay of older persons;

Secondary hypotheses:

a. The onset of a pneumonia event in institutionalized older residents is associated with higher healthcare costs;

b. Incident pneumonia events are associated with an increased risk of mortality in older persons living in nursing home;

c. The onset of a pneumonia event is responsible for a significant worsening of the physical function of nursing home residents;

Tertiary hypotheses:

a. Specific variables at patient- and nursing home-level may predict the severity of the pneumonia-related functional loss;

b. Nursing home residents dying due to pneumonia produce a significantly higher burden in terms of healthcare costs compared to nursing home residents dying for other causes.

Therefore, the INCUR project will pursue the following aims:

Primary aims:

a. To estimate the incidence of pneumonia events in a sample of older nursing home persons over a period of 12 months;

Secondary aims:

a. To compare the healthcare costs of nursing home older persons experiencing a pneumonia event versus those who will not over a period of 12 months;

b. To calculate the mortality risk in a sample of older residents living in nursing home according to the presence/absence of a pneumonia event occurred during a follow-up period of 12 months;

c. To measure the physical function modifications experienced by a sample of nursing home residents according to the presence/absence of a pneumonia event occurred during a follow-up period of 12 months;

Tertiary aims:

a. To identify sociodemographic, clinical, and biological characteristics of nursing home older residents, as well as environmental and organizational factors of their own hosting institution, which are associated with a higher degree of functional loss following a pneumonia event;

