## Methods/design

For the INCUR project, we recruited 800 residents of 13 nursing homes randomly selected in the Midi-Pyrénées region of France. In particular, nursing homes of the region were consecutively and randomly invited at participating in INCUR. After each nursing home accepted to be involved in the study, all its residents (according to their eligibility for INCUR) were assessed by the study personnel. The recruitment was conducted up to the reaching of the final sample of 800 participants according to the predefined sample size analyses (see specific paragraph). All the nursing homes were part of a national network of institutions representative of this healthcare in France [4]. To be part of the project, the director, the coordinating physician, and the responsible for the nursing of each institution signed a formal agreement and letter of support.

The main inclusion and exclusion criteria were the constituted by the score obtained by the participant at the *Autonomie Gérontologie - Groupes Iso-Ressources* (AGGIR) scale (Table 1). This scale allows to homogeneously generate six *Groupes Iso-Ressources* (GIR) at the French national level. The resulting GIR expresses the global functional capacity of the person and drives decisions about the provision of social support from public healthcare system. Subjects with severe disability are excluded from INCUR on the basis of the worst GIR group (i.e., 1). The reason for such exclusion resides in the impossibility to determine in these patients the weight of functional loss due to a pneumonia event (primary aim d). Similarly, residents with no sign of functional impairment at the AGGIR scale (that is having the maximum GIR score of 6) are excluded due to the incapacity to perceive possible functional improvement over the follow-up.

**Table 1 T1:** Inclusion and exclusion criteria of the INCUR study

*Inclusion criteria*	*-* Residents aged 60 years and older
	*- Groupes Iso-Ressources* (GIR) ranging between 2 (included) and 5 (included). This is the French administrative tool used to rate the ability of the person to be independent; it ranges from 6 (fully independent) to 1 (fully dependent, bed-ridden)
*Exclusion criteria*	- Residents living in the participating nursing homes for less than 30 days since the baseline study visit
	- Refusal of the patient and/or the family to participate at the INCUR project

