### Sample size analyses

Mehr and colleagues [25] estimated that the incidence of nursing home-acquired pneumonia in the United States may range between 0.3 to 2.3 episodes per 1,000 resident-days. In the present study, we expect to enroll 800 EHPAD residents and follow them over a 12-month period (i.e., a total of 292,000 resident-days). Considering the attrition due to mortality (i.e., 20% per year in this setting^4^), we may expect between 70.1 and 537.3 cases according to the Meher and colleagues’ data [25]. More recently, Rothan-Tondeur and colleagues [38] reported 311 infections in a sample of 2,140 nursing home residents over a period of 28 days (from January 24 to February 20, 2005). The study was conducted defining pneumonia according to the same criteria we will implement in INCUR. Authors showed that pneumonia represented the 7% of all the cases of infections (i.e., 22 events). Translating these figures over a 365-day period (as proposed in the INCUR project) and sample size we plan to recruit (i.e., 800 participants), we obtain 107.2 pneumonia events. It might happen that attrition due to mortality (i.e., 20% per year^4^) and the spring-summer seasons (during which the pneumonia events might be fewer; i.e., additional 40% over 6 months) may further reduce such estimation. However, we believe that, even in the worst case scenario (i.e., 68.6 cases of pneumonia over one year, consistent with the minimum estimation obtained from analyses performed on the Meher and colleagues’ data [25]), it will be possible the evaluation of a sufficient number of events to successfully accomplish the INCUR study aims. The recruited sample size of 800 participants produces a two-sided 98.2% or 95.2% confidence interval with a width equal to 0,050 when the incidence of pneumonia are 10% or 15%, respectively. Such incidence rates are overestimating the outcome of interest compared to the previous study by Rothan-Tondeur et al [38]. (7%); thus, INCUR study is adequately powered to accurately estimate the incidence of pneumonia with the sample of 800 participants.

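### The primary incidence is defined as a proportion of residents, which cannot supply the resident-day rate or the yearly event count that the plan says it will report

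*Protocol article*

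**What the plan says.** The only primary aim, under Hypotheses and objectives, is "To estimate the incidence of pneumonia events in a sample of older nursing home persons over a period of 12 months". Its target is events.

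Under Analysis plan, primary aim a, the estimator is "The ratio between the number of participants experiencing one or more events and the number of participants constituing the overall sample". Both numerator and denominator are counts of persons. The following sentence reads "Results will be presented as pneumonia cases per 1,000 resident-days, and as pneumonia events over one year". No resident-day denominator is given there, and nothing is said about second and later episodes.

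The Sample size analyses section works on both scales. Its expected case numbers start from resident-days: "we expect to enroll 800 EHPAD residents and follow them over a 12-month period (i.e., a total of 292,000 resident-days"), with a cited incidence that "may range between 0.3 to 2.3 episodes per 1,000 resident-days", reduced for 20% yearly mortality. Its precision statement is for a proportion among 800 residents, at 10% and 15%. The Analysis plan repeats the mortality figure: "expected mortality about 20% over 12 months, that is 160 fatal events in our sample population". Censoring at death or last contact is written only for the mortality comparison, secondary aim b.

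**The concern.** One sentence fixes a proportion of persons, and the next announces two quantities that need different ingredients. A rate per 1,000 resident-days needs the time actually observed, which is shorter than a year for anyone who dies. A count of events over a year needs every episode, not every affected resident.

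An analyst who follows the text has to improvise the step from ratio to rate. The obvious improvisations do not give an episode rate like the ones the study cites as benchmarks. This is the only primary result, and the Discussion says the study will support sample size calculations for future trials, so readers will reuse the figure.

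**Working it through.** **The plan's own figures reproduce.**
- Expected cases: 0.3 × 292 × 0.8 = 70.1 and 2.3 × 292 × 0.8 = 537.3.
- Second source: 22 / 2,140 × 800 × 365 / 28 = 107.2 events. The worst case is 107.2 × 0.8 (mortality) × 0.8 (40% fewer over half the year) = 68.6.
- Precision: with half-width 0.025 and n = 800, z = 0.025 / √(p(1−p)/800). This is 2.357 at p = 0.10 (98.2%) and 1.980 at p = 0.15 (95.2%).

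The expected cases are on an episode and resident-day scale. The precision is on a person-proportion scale.

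**Inputs for the check**, all from the Sample size analyses section:
- Episode rates of 0.30 and 2.3 per 1,000 resident-days (the cited range).
- 22 / (2,140 × 28) × 1,000 = 0.367 per 1,000 resident-days, implied by the source that used the same pneumonia criteria. With the plan's seasonal factor it is 0.367 × 0.8 = 0.29, close to the lower end of the range.
- Mortality of 20% per year.

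**Assumptions (mine):** constant episode rate L per year, constant death hazard m = −ln(0.8) = 0.2231 per year, independent episodes, death unrelated to pneumonia, no other loss.

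**Formulas**
- Mean time lived in the year: (1 − e^(−m)) / m = 0.2 / 0.2231 = 0.896 year. For 800 residents this is about 261,700 resident-days, not 292,000. Deaths spread evenly over the year give 262,800.
- The plan's ratio: P = L/(L+m) × (1 − e^(−(L+m))).
- All episodes: 800 × L × 0.896.
- Conversion A, full follow-up: P / 365 × 1,000.
- Conversion B, observed time: 800 × P / 261,700 × 1,000.

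**Results**

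| True rate per 1,000 | L per year | P | Residents affected | All episodes | Conversion A | Conversion B |
|---|---|---|---|---|---|---|
| 0.300 | 0.1095 | 0.0931 | 74.5 | 78.5 | 0.255 (−15%) | 0.285 (−5%) |
| 0.367 | 0.1340 | 0.1127 | 90.2 | 96.1 | 0.309 (−16%) | 0.344 (−6%) |
| 2.300 | 0.8395 | 0.5170 | 413.6 | 601.9 | 1.417 (−38%) | 1.580 (−31%) |

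Treating those who die as followed for the whole year costs 1 − 0.896 = 10.4% in every row. Counting each resident once costs the 5%, 6% and 31% under conversion B. The two multiply: in the first row, 0.896 × 0.949 = 0.85.

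All episodes divided by observed resident-days returns the true rate in every row. So does first episodes divided by time to first episode, under the constant-rate assumption.

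**The case against.** The ratio is a sound estimate in its own right. If follow-up ends only at death or 12 months, residents with at least one event over all enrolled is the cumulative incidence of a first pneumonia with death as a competing event. Keeping early deaths in that denominator is then correct. The ratio also matches the precision statement, which is for a proportion. This stands, and the ratio should be kept.

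A reader might infer that the plan is bound to understate the rate. The document does not support that. It never states a division by 365 days for every enrolled resident. The two sentences can be read as announcing several measures, with the rate to be computed separately from episodes and observed time. On that reading there is no bias, but the rate would then rest on a numerator and a denominator that both differ from the only definition given.

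The 38% should not be the headline either. It belongs to the top of the cited range, while the source with the same criteria points to 107.2 events, or 68.6 in the worst case. With that many events, a simple Poisson 95% margin is 1.96/√107.2 = 19% to 1.96/√68.6 = 24%, so a 5 to 16% shortfall is smaller than the sampling error. That limits the practical weight but does not excuse the definition: the shortfall is systematic and does not shrink with more data.

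**Conclusion.** The point holds as a mismatch between definition and reporting scale. As written, the primary estimator is a 12-month cumulative risk and cannot yield cases per 1,000 resident-days or events over one year.

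If the ratio is nevertheless put on a resident-day scale, the shortfall against the episode rate is about 15 to 16% with full follow-up as denominator, and about 5 to 6% with observed resident-days, at 0.30 to 0.37 per 1,000. At 2.3 per 1,000 it is 38% and 31%. These sizes rest on constant rates, independent episodes, death unrelated to pneumonia and 20% annual mortality. The plan's own secondary hypothesis links pneumonia to death, so they are indicative. Repeat episodes that cluster in the same residents would widen the gap between residents affected and episodes. The documents do not establish that the published rate will be too low, only that the stated formula does not define it.

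**What to change.** Replace the single definition under primary aim a with two labelled estimates:

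1. **Incidence rate:** all new pneumonia episodes divided by the resident-days actually observed, from baseline to death, last contact or 12 months, per 1,000 resident-days. The count of events over one year uses the same numerator.
2. **Twelve-month cumulative incidence of a first pneumonia**, with death as a competing event. This is the existing ratio when there is no loss other than death. State that the precision figures in the Sample size analyses section apply to this estimate.

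Compare only the first with the cited episode rates. The cost is wording and analysis code. The mortality analysis already needs the dates of death and last contact, and the physical function analysis already needs the date of pneumonia onset. The sample size and visits are unchanged. The one practical check is that onset dates are recorded for repeat episodes as well as first ones.

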b. To explore whether mortality due to pneumonia is associated with higher healthcare costs compared to death events due to non-respiratory causes in nursing home older residents.

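### Secondary aim a compares one-year cost totals between residents classed after the fact as ever or never having pneumonia, with no allowance for time alive or event timing

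*Protocol article*

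**What the plan says.** Under Analysis plan, Secondary aims, a, the article names the cost variable: "Primary independent variable of interest for the present analyses will be the total expenditure (in Euros) that participants will cost" the healthcare system over the follow-up year. It then fixes the grouping: "All these analyses will be stratified and compared according to the presence/absence of pneumonia events". The models follow: "Unadjusted and adjusted analyses of covariance, logistic regression models, and multinominal logistic regression models will be performed", with outcomes "predicted by the absence/presence of pneumonia events occurred during the follow-up (dicothomous independent variable of interest". So the outcome (one-year euros), the exposure (a yes/no flag that is complete only when follow-up ends) and the model family are all stated. No term for days alive, date of onset or a post-onset cost window is mentioned.

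The same document expects about 20% mortality over 12 months, or 160 deaths (Analysis plan, Tertiary aims, b). Its secondary hypothesis b is that pneumonia raises mortality. The opening of Hypotheses and objectives describes the economic question in terms of resource use that comes after the pneumonia.

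Tertiary aim b compares total expenditure among residents who die, by cause of death. "These analyses will consider the entire follow-up period available", with a secondary analysis limited to the last month of life. The aim asks whether "mortality due to pneumonia is associated with higher healthcare costs compared to death events due to non-respiratory causes". The tertiary hypothesis b and the analysis text take all other causes of death as the comparator.

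**The concern.** A one-year total is the product of how long a resident lives and how much is spent per day. The ever/never flag is tied to the first factor in three ways.

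- **Selection on survival.** Nobody can be classed as exposed without living to the onset date. Residents who die early without pneumonia fall into the never group.
- **Truncation by death.** If pneumonia shortens life, as the protocol hypothesises, the exposed group stops accruing cost sooner.
- **Cost before the event.** All spending from baseline to onset is counted in the pneumonia group, although it cannot be a consequence of the pneumonia.

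The first raises the pneumonia group's total relative to the other and the second lowers it. The third mixes in spending unrelated to the event. Baseline covariates cannot correct a grouping that depends on what happens after baseline. At stake is the reported cost of pneumonia, the first secondary aim: a difference could appear with no cost effect, or a real one could be masked.

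The physical-function analysis (secondary aim c) does compare before with after and adjusts for days since onset. The cost analysis does neither.

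**Working it through.** **The article's own figures.** 800 × 365 = 292,000 resident-days; 800 × 0.20 = 160 deaths; (22 / 2,140) × 800 × (365 / 28) = 107.2 pneumonias. All reproduce.

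**Inputs**
- Pneumonia rate from Sample size analyses: 22 / (2,140 × 28) = 0.367 per 1,000 resident-days, so λ = 0.367 × 365 / 1,000 = 0.134 per year. The cited range is 0.3 to 2.3.
- Mortality: 20% at 12 months overall.
- Assumed: constant hazards, the same daily cost for everyone (no true cost effect), and a death hazard multiplied by HR after onset. The article gives no HR, so 1, 2, 3 and 5 are tried.

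With equal daily cost, the ratio of mean totals equals the ratio of mean time alive within the year.

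**Formulas** (h = death hazard before pneumonia, s = λ + h, k = HR × h; integrals over u from 0 to 1)
- P(ever) = (λ/s)(1 − e^(−s))
- Ever group, time before onset: ∫ u λ e^(−su) du / P(ever)
- Ever group, time after onset: ∫ λ e^(−su) (1 − e^(−k(1−u)))/k du / P(ever)
- Never group, time alive: [∫ u h e^(−su) du + e^(−s)] / (1 − P(ever))
- h is set so that overall mortality is 20%.

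**HR 1 in full.** h = −ln(0.8) = 0.2231 and s = 0.3571, so P(ever) = (0.134 / 0.3571)(1 − 0.6997) = 0.113. Ever group: 0.470 years before onset and 0.492 after, 0.962 in total. Never group: (0.0882 + 0.6997) / 0.887 = 0.888 years. Ratio 0.962 / 0.888 = 1.08. Check: 0.113 × 0.962 + 0.887 × 0.888 = 0.896, which equals the overall mean 0.20 / 0.2231 = 0.896.

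| Assumed HR | h | Years alive, ever | Years alive, never | Cost ratio | Share of ever-group time before onset |
|---|---|---|---|---|---|
| 1 | 0.2231 | 0.962 | 0.888 | 1.08 | 49% |
| 2 | 0.2105 | 0.931 | 0.894 | 1.04 | 51% |
| 3 | 0.2003 | 0.906 | 0.899 | 1.01 | 52% |
| 5 | 0.1849 | 0.866 | 0.906 | 0.96 | 55% |

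**Sensitivity.** At 0.3 per 1,000 resident-days the ratios agree with the table to within 0.01. At 2.3 they are 1.15, 1.08, 1.04 and 0.99. If instead 20% or 40% of cases die within 30 days of onset and there is no later effect (rate 0.3, simulated), the ratio is 0.98 or 0.87.

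**Decedents (tertiary aim b).** In those last two simulations, mean time alive among those who died was about 0.50 years for pneumonia deaths and 0.48 for others. Varying follow-up then mainly adds noise; it would bias the comparison only if the timing of death differed by cause. About 8% to 9% of deaths fell in the first 30 days, where a last-month window would be incomplete.

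**The case against.** The aim is to compare costs over 12 months, and the hypothesis speaks of association. As a description of what the insurer spends in a year, a dead resident's later cost is truly zero, not missing; a per-day-alive figure answers a different question and conditions on survival. This stands, and it is why the annual total should be kept as a descriptive figure. It does not rescue the contrast as a measure of the consequences of pneumonia, which is how the article frames it.

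The distortion may also be small beside sampling error. With about 107.2 × 0.8 = 86 cases and an assumed coefficient of variation of cost of 0.5 to 2, the relative standard error of the pneumonia-group mean is 0.5/√86 = 5% to 2/√86 = 22%. This also stands for the survival component. It does not remove the pre-event cost, which covers about half of the group's time.

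Several stronger readings are tempting but unsupported:
- That the comparison is wholly unadjusted. Adjusted models are planned, and leaving their covariates to a fuller document is normal for an article.
- That log-transformation or rank tests defeat the main cost question. Those methods are stated only for the tertiary aims; secondary aim a speaks of means and risks.
- That the decedent comparison is biased by date of death. No difference in timing by cause is given, and a last-month analysis is already planned.
- That calling cost the independent variable changes the model. The next paragraph gives that role to pneumonia; it is a wording slip.

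**Conclusion.** The point holds for secondary aim a. As written, outcome, grouping and model together mix survival and pre-event spending into the reported cost of pneumonia, and covariate adjustment at baseline cannot separate them. With equal daily cost and 20% mortality, the ever/never ratio runs from about 1.08 (no effect on death) to 0.96 (HR 5). It reaches 1.15 at the highest cited pneumonia rate and 0.87 if 40% of cases die within 30 days. About half of the pneumonia group's person-time, and of its cost if daily cost is constant, precedes onset.

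A reader might infer that the plan overstates the cost of pneumonia by 8%. The document does not support that: the figure requires no effect on mortality, contrary to the protocol's own hypothesis, and the sign can reverse. All sizes rest on constant hazards, constant daily cost and assumed mortality effects; cost concentrated near death would change them. For tertiary aim b, only a presentation point and an inconsistent comparator remain. The primary aim is unaffected.

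**What to change.** **Secondary aim a.** Do one of the following:
- Split each resident's insurer costs by calendar period and enter pneumonia as a time-updated exposure.
- Compare costs over fixed windows from onset with those of event-free residents alive at a matched index date.

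Adjust for pre-event cost in either case. Report the mean euro difference with its interval, and show survival beside it so that a low cost due to early death is visible. Keep the annual total by ever/never pneumonia as a descriptive figure. The exact model is open; several would serve. Call expenditure the dependent variable.

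**Tertiary aim b.** Report cost per day alive, or the last-month window already planned, beside the whole-follow-up total. Use one comparator, non-respiratory or all other causes, in the hypothesis, aim and analysis.

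**Cost.** No new recruitment or visits. The work is analysis wording and more data handling, plus a dated insurer extract for all 800 residents. The last-month analysis already implies dated costs for those who die, but the Healthcare costs section promises total and detailed expenditure without saying that it will be dated for everyone. This should be confirmed with the insurer.

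### Secondary aim a compares total yearly cost by pneumonia yes/no without accounting for time alive, so survival time confounds the cost comparison in a direction the protocol cannot determine

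*Protocol article*

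**What the plan says.** In the Analysis plan, secondary aim a, the cost variable is "the total expenditure (in Euros) that participants will cost to the healthcare system over the follow-up year". On grouping the plan says: "All these analyses will be stratified and compared according to the presence/absence of pneumonia events". Group membership is settled after baseline, since outcomes are to be "predicted by the absence/presence of pneumonia events occurred during the follow-up (dicothomous independent variable of interest". The methods are also named: "Unadjusted and adjusted analyses of covariance, logistic regression models, and multinominal logistic regression models will be performed".

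For this aim the article mentions no days alive, offset, censored-cost method or time-dependent exposure. The only censoring rule in the Analysis plan belongs to secondary aim b, the mortality analysis.

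Elsewhere the protocol expects substantial mortality. The sample size section reads: "Considering the attrition due to mortality (i.e., 20% per year in this setting". Tertiary aim b turns this into 160 deaths. Secondary hypothesis b states: "Incident pneumonia events are associated with an increased risk of mortality in older persons living in nursing home".

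**The concern.** A resident's yearly total depends on how many days of the year the resident is alive. Two features of the design make those days differ between the groups for reasons unrelated to the cost of treating pneumonia.

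- **Guaranteed survival to onset.** Someone who dies in month two without pneumonia is in the comparison group for good. Someone with pneumonia in month nine has, by definition, lived nine months. This inflates the pneumonia group's total even if pneumonia harms nobody, and the group is also credited with its costs before onset.
- **Truncation by death.** Residents who die of pneumonia stop generating routine cost, which lowers the pneumonia group's total. Secondary hypothesis b expects such deaths.

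The article says the study is designed to estimate the economic consequences of pneumonia. A difference in totals could support or contradict the cost hypothesis with no difference in cost per day of life, and no known sign is available to correct it afterwards.

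**Working it through.** **1. The plan's own figures.**
- Deaths: 800 × 0.20 = 160, as stated.
- Pneumonias before attrition: 22 / 2,140 / 28 × 365 × 800 = 107.2, as stated.
- Worst case: 107.2 × 0.8 × 0.8 = 68.6, as stated.
- Pneumonia-related deaths: 160 × 0.07 = 11.2, as stated. The 7% is pneumonia's share of infections in the cited survey, so 11.2 is a rough figure.

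**2. Rates used.**
- Death hazard: −ln(0.80) = 0.223 per year.
- Pneumonia hazard: 107.2 / 800 = 0.134 per year.
- Crude case fatality: 11.2 / 107.2 = 10.4%, and 11.2 / 68.6 = 16.3%.

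**3. Days alive in each group.** Assumptions not in the protocol: constant hazards, the same constant daily cost for everyone, and extra deaths falling within 30 days of onset on top of background mortality. With equal daily cost, the ratio of mean total cost equals the ratio of mean days alive. Simulation of millions of residents gives:

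| Added 30-day case fatality | Source of the value | Ratio of mean days alive, pneumonia / none | Spurious cost difference |
|---|---|---|---|
| 0% | reference | 1.083 (351 v 324 days) | +8% |
| 10% | about the protocol's 10.4% | 1.03 | +3% |
| 16.3% | protocol-derived | 1.00 | about 0% |
| 20% | assumed | 0.98 | −2% |
| 30% | assumed | 0.93 | −7% |
| 40% | assumed | 0.88 | −12% |

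The 0% row can be confirmed by direct integration: 351.0 v 324.1 days, ratio 1.083.

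**4. Dependence on the cost of dying.** A second simulation fixed overall mortality at 20%, set the pneumonia hazard at 0.10 per year and varied the hazard ratio (HR) for death after pneumonia. All cost inputs are assumed. The entries are the planned difference in total cost, pneumonia minus none, in days of routine cost, when a pneumonia episode itself costs nothing:

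| Cost of a death (routine days) | HR 1 | HR 2 | HR 3 | HR 5 |
|---|---|---|---|---|
| 0 | +26.5 | +13.6 | +2.6 | −15.2 |
| 90 | +17.4 | +13.1 | +9.2 | +2.3 |
| 180 | +8.4 | +12.5 | +15.9 | +19.8 |

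The difference falls with lethality when routine accrual dominates, and rises with it when dying is expensive.

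**5. Cost per resident-day alive.** With no episode or death cost it returns 1.00 v 1.00 at every HR, which is correct. With an episode cost of 60 and no death cost it gives 1.17 v 1.00 at HR 1 and 1.19 v 1.00 at HR 5. With an episode cost of 60 and a death cost of 180 it moves from 1.23 v 1.12 at HR 1 to 1.41 v 1.10 at HR 5. It is therefore not free of lethality when dying is costly.

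**The case against.** The strongest defence is that total payer cost over a fixed year is a legitimate quantity. Secondary aim a is worded as a comparison of costs over 12 months, the Healthcare costs section speaks of what the public system is charged, and spending that ends at death is a true part of that charge. This stands as a reason to keep the total. It does not make the ever/never difference a measure of what pneumonia costs, because that difference includes costs before onset and guaranteed survival to onset.

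A second defence is that the covariates of the adjusted models are not listed and may be set in a fuller plan. That is fair for covariates, but outcome, grouping and model type are already fixed here. Entering survival time as a covariate would not move the pre-onset cost out of the pneumonia group.

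A third is that the size is modest on the protocol's own figures. That stands: +3% to 0% under equal daily cost.

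A reader might also infer something stronger: that the more lethal pneumonia is, the cheaper it will look, or that if hypothesis b is true the analysis is biased against finding a cost. The protocol does not support either. At 10% added case fatality pneumonia clearly raises mortality, yet the bias is still upward. The trend reverses if dying is costly, and tertiary aim b itself allows that costs may be compressed into the last period of life. Nor is a survival difference between the groups an established fact in the protocol; it is a hypothesis.

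**Conclusion.** The point holds as a confounding problem of undetermined direction. The stated analysis attributes to pneumonia a cost difference that partly reflects how long residents in each group lived. Under equal constant daily cost the distortion runs from +8% (no added fatality) through +3% to 0% (protocol-implied fatality) to −12% (an assumed 40%). The negative values need case fatalities of about 20% or more, which the protocol does not give, and the 10% to 16% range itself rests on the rough 11.2 deaths. No cost figure is available to say whether routine accrual or the cost of dying dominates. It matters because this is a named secondary aim and its result could not be corrected after the fact. It does not touch the primary aim.

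**What to change.** Keep total yearly cost by group as the payer's annual figure, and report survival in each group beside it.

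For the hypothesis that pneumonia raises costs, add an analysis of cost per resident-day alive with pneumonia as a time-dependent exposure. Divide each resident's follow-up into short periods, for example 30 days. Count time and cost before onset as unexposed and move the resident to exposed from the onset date. Model cost per period with days alive as an offset, and report the ratio or difference in cost per day alive.

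The cost is mainly programming and a few sentences in the plan. The one data condition is dated expenditure for all residents. The Healthcare costs section promises total and detailed expenditure, and the last-month analysis in tertiary aim b implies dated costs for decedents, but dated records for everyone are not stated and should be confirmed with the insurer. Because cost per day alive also varies with lethality when dying is costly, it should be read together with total cost and survival.
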